### Predictors

Definitions and timing of the predictor variables for the eight models were extracted from original publications (Table 1). Recorded variables in the cohorts are matched, as closely as possible, to the original predictor measurement procedures (Supplementary file 3).

### Statistical analysis

We will externally validate the eight COVID-19 prognostic models in the six cohorts of older patients with COVID-19, aiming to assess their predictive performance when transported from a general adult population to a specific older population. The performance of the GAL-COVID-19 model is assessed across the three healthcare settings. The GAL-COVID-19 mortality model was developed in a primary care setting (general practitioners) and will be validated across different settings (in hospitals, primary care, and nursing homes) [26]. The 4C Mortality Score, NEWS2 + model, Xie model, Wang clinical model, APACHE-II score, CURB-65 score, and SOFA score were developed in hospitalized populations and will be externally validated in the same setting. Evaluation and assessment of the predictive performance of the COVID-19 prognostic models will be performed in each cohort separately. The statistical analysis will be performed in R (version 4.0.0 or later) [27].

#### Descriptive analysis

Participant characteristics and predictor information will be described in all study cohorts (overall and stratified on mortality outcome status) to identify differences in case-mix between the development and validation study populations [28]. These comparisons give insight into the expected model performance and transportability [26].

#### Missing data

The missing data will be described to determine possible reasons for and patterns in missingness [29]. Based on these findings, decisions about the handling of the missing values in the statistical analysis will be made. We anticipate that missing data will be handled using multiple imputations by chained equations using the Full Conditional Specification or Joint Modelling (JOMO) [30]. All variables and outcomes in the final prognostic models are included in the imputation model to ensure compatibility. A total of 50 imputed datasets will then be generated as cohorts are expected to have less than 50% missing values for all relevant variables [31].

#### Assessment of predictive performance

For each prognostic model, we will apply the model according to the authors’ original descriptions and evaluate its predictive performance. We will evaluate discrimination (the model’s ability to distinguish individuals who died after presentation with COVID-19 diagnosis from those who did not) and calibration (the agreement between predicted and observed mortality risks) in each cohort [32]. Discrimination will be assessed in all models by quantifying the area under the receiver operating characteristic curve, i.e., c-statistic [33], and pooled by taking the median c-statistic over imputed datasets and computing dispersion using the interquartile range [34].

Calibration will be assessed by visualizing the calibration of expected versus observed risk using LOESS-smoothed plots on stacked imputed data sets [35]. The GAL-COVID-19 mortality model, NEWS2 + model, Xie model, and Wang clinical model are model equations. For these models, calibration will be assessed in terms of the calibration-in-the-large coefficient and calibration slope [35]. The coefficients are again pooled on a log scale using Rubin’s rules in case of multiple imputed datasets [36]. For each performance measure, for each evaluated model, we will compute the point estimate, standard error, and 95% confidence interval.

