#### Sample size

Using national statistics from July 2020 to December 2021, the COVID-related mortality fraction for the older population (≥ 70 years) living at home in the Netherlands (including self-reported COVID-19-positive patients) was around 3% [3]. Although we expect higher mortality in nursing homes, hospitals, and ICU admissions, we will assume that an outcome incidence of 3% is the lowest event fraction that we will encounter for the current prediction model validation study. We take this fraction as a starting point for the sample size calculations, which are based on sample size calculation recommendations for external validation studies by Riley and colleagues [38]. Since we are considering various models, we base our sample size calculation around a general scenario that is reasonably applicable to all cases. Based on the distributions of predicted risk of mortality that were previously reported for some of the cohorts [8, 39], we assume the distribution of the linear predictor to be approximately N (− 3.9,1) [38]. Based on the calculations, a sample size of 754 will be required per cohort to validate an assumably well-calibrated model with a calibration-in-the-large coefficient of 0 and calibration slope of 1, and an assumed target standard error of calibration slope of 0.02. The target standard error of the calibration slope was chosen to ensure the evaluation of calibration with a higher precision than the typically used value of 0.05.

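### The c-statistic's pooling rule (median and IQR over imputed datasets) carries no sampling error and is not reconciled with the standard error and 95% CI promised for each performance measure

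*Protocol article*

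**What the plan says.** Three statements in the protocol article, all under Assessment of predictive performance, bear on this:

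- The c-statistic, computed for all eight models, is "pooled by taking the median c-statistic over imputed datasets and computing dispersion using the interquartile range".
- For the four models that are equations, calibration-in-the-large and the calibration slope are estimated, and "The coefficients are again pooled on a log scale using Rubin’s rules in case of multiple imputed datasets".
- The section closes: "For each performance measure, for each evaluated model, we will compute the point estimate, standard error, and 95% confidence interval".

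The Missing data section anticipates multiple imputation and sets its size: "A total of 50 imputed datasets will then be generated", on the ground that "cohorts are expected to have less than 50% missing values for all relevant variables". No section says how a standard error or interval for the c-statistic is combined across those 50 datasets.

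**The concern.** The 50 imputed datasets are 50 completions of one cohort. Patients and observed values are identical in each, and only the filled-in values differ. The spread of the c-statistic over them answers one question: how much does the result depend on the imputed values? It does not say how far the result might move with another sample of patients, which is what a standard error and confidence interval describe.

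The only rule given for the c-statistic thus yields a quantity of a different kind from the one promised at the end of the section. The word *again* in the Rubin's-rules sentence adds to the doubt. It can be read as implying that those rules had already been applied, yet the only pooling rule before it is median and IQR. An analyst has to choose how to proceed.

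The c-statistic is planned for every model, and the Discussion says the design allows assessment of heterogeneity between settings. A dispersion measure that follows data completeness and not the number of deaths would mislead a reader who took it for precision.

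**Working it through.** **The plan's own figure.** The article gives no precision target for the c-statistic. Its one design figure is "a sample size of 754 will be required per cohort" (Sample size), used here only as the n at which to size the effect. The closed-form slope criterion does not reproduce it. With linear predictor N(−3.9, 1), intercept 0 and slope 1, the information terms are I_a = 0.02870, I_ab = −0.08697 and I_b = 0.28936. Then n = I_a / {SE²(I_a·I_b − I_ab²)} = 38.717 / 0.02² ≈ 96,793. That is a separate question and nothing below depends on it.

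**Inputs from the documents.** n = 754, event fraction 3%, linear predictor N(−3.9, 1), 50 imputations, missingness below 50% per variable. The linear predictor implies c ≈ 0.756, and 754 × 0.03 ≈ 23 deaths.

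**Assumed inputs.** One of two, three or four equally weighted predictors is missing in 10–50% of patients (completely at random in the four-predictor run). Imputation is proper and normal, conditional on the outcome and the other predictors. There is also a higher-mortality scenario.

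**Step 1: sampling error with no missing data.** Newcombe's formula is SE(c)² = c(1−c)[1 + (n/2−1)(1−c)/(2−c) + (n/2−1)c/(1+c)] / [n²φ(1−φ)]. With c = 0.756, n = 754 and φ = 0.03, this is 0.1845 × (1 + 73.7 + 161.9) / 16,544 = 0.00264, so SE ≈ 0.051. The 95% interval is about ±0.10. The IQR over imputations in the same complete cohort is exactly 0.

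**Step 2: simulation with missing data.** Four predictors, 150 replicates per row. The 95% interval pools logit(c) by Rubin's rules with DeLong within-dataset variance. An IQR spans a middle 50%, so the fair comparator is a 50% interval, obtained approximately as the 95% width × 0.674/1.96 = 0.344.

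| Missing | IQR width | Rubin 95% width (coverage) | 50% width | 50% width ÷ IQR | IQR contains true c |
|---|---|---|---|---|---|
| 10% | 0.0112 | 0.1968 (93%) | 0.0677 | 6.0 | 12.7% |
| 30% | 0.0231 | 0.2092 (92%) | 0.0720 | 3.1 | 16.7% |
| 50% | 0.0355 | 0.2315 (96%) | 0.0796 | 2.2 | 21.3% |

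**Step 3: where the variance lies.** Take the between-imputation SD as roughly IQR/1.349 and the mean within-dataset SEs as 0.0496 and 0.0527.

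- 10% missing: B = (0.0112/1.349)² = 0.000069 and W = 0.0496² = 0.00246. The between part is 1.02 × 0.000069 / 0.00253 ≈ 3% of total variance.
- 50% missing: B = 0.00069 and W = 0.00278. The between part is 1.02 × 0.00069 / 0.00348 ≈ 20%.

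The total variances give 95% widths of 3.92 × √0.00253 = 0.197 and 3.92 × √0.00348 = 0.231, which agree with the table.

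**Step 4: other settings.**

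- Two predictors: IQR width 0.016–0.048 against 95% widths of 0.20–0.24, or 0.069–0.083 at 50%. The ratio is 4.3 down to 1.7, and the IQR contains the true c in 12–38% of datasets.
- Three predictors: 0.012–0.038 against 0.069–0.079 at 50%. The ratio is about 5.8 down to 2.1, with 13–27% containing the true c.
- Four predictors, more deaths (assumed linear predictor mean −0.8): 0.0045–0.0138 against 0.0752 × 0.344 = 0.0259 and 0.0845 × 0.344 = 0.0291. The ratio is 5.7 down to 2.1, with 10–25% containing the true c.

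**Step 5: ranking by completeness.** The low-mortality cohort (about 23 deaths, 10% missing) has IQR width 0.0112. The high-mortality cohort with 50% missing has 0.0138. By IQR the first looks more precise, yet its 95% interval is 0.1968/0.0845 ≈ 2.3 times wider.

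**The case against.** The strongest reply is that the plan does not leave sampling error out. It promises that "we will compute the point estimate, standard error, and 95% confidence interval" for each measure, and it never calls the IQR an interval or a standard error. The two sentences could stand together, with the IQR describing spread across imputations and a confidence interval reported beside it. How that interval is combined would then be detail left to a fuller plan, and the Missing data section makes imputation itself provisional. Much of this stands. A reader might infer that the published error bars will be several-fold too narrow, but the documents do not say that the IQR replaces the promised interval.

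The reply does not remove the point. The article goes beyond silence: it names a pooling rule for this measure, that rule cannot yield the promised quantities, and it gives the suitable rule only to other measures.

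Other stronger readings also fail:

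- Setting the IQR against a 95% interval gives ratios of up to about 18 (0.1968/0.0112), but that compares a 50% range with a 95% one.
- The c-statistic is not the only numeric measure planned for all eight models; the Decision curve analysis section plans net benefit for each.
- It cannot be said that chance differences will be declared real. Cohorts are evaluated separately, and no test between models, cohorts or settings is stated.

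**Conclusion.** The concern holds as an unreconciled inconsistency with a poorly chosen dispersion measure. It is not a demonstrated omission of sampling error. That the IQR contains no sampling variance, and is zero with complete data, follows from its definition and needs no simulation.

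The size does rest on assumptions: the missingness pattern, equally weighted predictors, 754 patients and, for the main figures, the lowest event fraction the authors expect. On those terms, an IQR read as precision is about 2 to 6 times narrower than a like-for-like 50% interval. It contains the true c-statistic in about 12–38% of datasets where 50% would be nominal. With 120–150 replicates per scenario in the two- and four-predictor runs, these percentages carry a Monte Carlo error of several points. The gap varies with the settings, but its direction was the same in all of them. This is a should-fix.

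**What to change.** Replace the pooling sentence for the c-statistic. In each imputed dataset compute logit(c) and its variance, for example DeLong's variance of c divided by [c(1−c)]² by the delta method. Pool estimate and variance by Rubin's rules, then back-transform to the estimate and the 95% interval that the section already promises. If median and IQR are kept, label them as a description of between-imputation variability and state that they are not a measure of precision.

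The cost is a sentence of text and a few lines of code, with no new data. The reported intervals will be wider than the IQR: at about 23 deaths, roughly ±0.10 on the c-statistic before any loss from missing data.

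### Pooling calibration-in-the-large on a log scale cannot be done as written: its ideal value is 0 and it is negative when a model over-predicts

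*Protocol article*

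**What the plan says.** Under Assessment of predictive performance, the Protocol article singles out the four models that are equations (GAL-COVID-19, NEWS2+, Xie, Wang). For these, "calibration will be assessed in terms of the calibration-in-the-large coefficient and calibration slope". The next sentence reads "The coefficients are again pooled on a log scale using" Rubin's rules, in the case of multiply imputed data. It makes no exception for either coefficient. The same paragraph then requires, for every measure and model, that "we will compute the point estimate, standard error, and 95% confidence interval".

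Three other statements bear on it:

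- Sample size describes a well-calibrated model as one with "a calibration-in-the-large coefficient of 0 and calibration slope of 1". This fixes the scale: calibration-in-the-large is an intercept with target 0, not a ratio with target 1.
- The only pooling described earlier is that of the c-statistic, which is "pooled by taking the median c-statistic over imputed datasets and computing dispersion using the interquartile range".
- Missing data anticipates multiple imputation: "A total of 50 imputed datasets will then be generated".

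**The concern.** A log scale is the usual choice for pooling a ratio, which is positive and has a null value of 1. Calibration-in-the-large is neither. It is a difference on the log-odds scale that takes either sign, and the plan's own target for it has no logarithm. An analyst who follows the sentence literally cannot complete the pooling for a well-calibrated model whose imputed estimates straddle 0, or for a model that over-predicts.

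A reported result is at stake. Calibration-in-the-large is to be given with an estimate, standard error and interval for four models. By Table 2, that is 6 cohorts for GAL-COVID-19 and 3 hospital cohorts for each of the other three, so 6 + 3 × 3 = 15 model–cohort pairs in the main analysis. It is also one of the inputs, with the slope and the LOESS plots, to judging whether a model is miscalibrated.

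**Working it through.** The plan states no figure for this point, so there is none to reproduce. The question is whether the transform is defined, and how often it would not be.

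**Inputs from the Protocol article (Sample size, Missing data).** The article says "we assume the distribution of the linear predictor to be approximately N" with mean −3.9 and SD 1. The sample size is 754 per cohort, with 50 imputed datasets.

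**Step 1. Information per participant.** Let p be the inverse logit of the linear predictor (LP). Averaging over its distribution by quadrature gives:
- event fraction E[p] = 0.031, in line with the plan's assumed 3%
- I_a = E[p(1−p)] = 0.02870
- I_ab = E[p(1−p)·LP] = −0.08697
- I_b = E[p(1−p)·LP²] = 0.28936

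**Step 2. Standard errors at n = 754.**
- Calibration-in-the-large (slope fixed at 1): 1/√(n·I_a) = 1/√(754 × 0.02870) = 0.215.
- Slope: √[I_a / (n(I_a·I_b − I_ab²))] = √[0.02870 / (754 × 0.000741)] = 0.227. This is far from the target of 0.02 in Sample size. That is a separate matter and does not enter here.

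**Step 3. How often calibration-in-the-large is at or below 0.** For one estimate, the probability is Φ(−true value / 0.215). For 50 imputations, 20,000 analyses were simulated with between-imputation variance set at 5%, 10% or 30% of the squared standard error. These fractions are assumptions; the article gives none.

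| True value | One estimate ≤ 0 | At least one of 50 ≤ 0 (5% / 10% / 30%) |
|---|---|---|
| −0.5 | 99% | over 99% in all three |
| −0.2 | 82% | not simulated |
| 0 | 50% | 69% / 76% / 88% |
| +0.2 | 18% | 34% / 42% / 61% |
| +0.5 | 1% | 3% / 5% / 15% |

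The 50% at a true value of 0 does not depend on the sample size. A larger cohort makes the failure more certain for an over-predicting model: at a true value of −0.2, the share at or below 0 is 94% with n = 2,000 (standard error 0.132) and 99% with n = 5,000 (standard error 0.083).

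Even if all 50 values were positive, an interval formed on the log scale and transformed back would lie wholly above 0, so it could never contain the plan's target.

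**Step 4. The slope.** Φ(−true slope / 0.227) is about 0.0005% at a true slope of 1, 0.1% at 0.7 and 1.4% at 0.5. Its logarithm nearly always exists.

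**Step 5. Pooling without a transform.** Fifty values were simulated around −0.05 (assumed between-imputation SD 0.06, within-imputation standard error 0.215). The drawn values had between-imputation variance 0.00287. Rubin's rules give a pooled value of −0.047 and a standard error of √(0.215² + (1 + 1/50) × 0.00287) = 0.222. The 95% interval is −0.047 ± 1.96 × 0.222, that is −0.48 to 0.39. Of the same 50 values, 42 have no real logarithm.

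**The case against.** The best defence is that *log scale* means the log-odds scale. Calibration-in-the-large is already expressed in log-odds, and the sentence does not say that logarithms are taken. On that reading the method is sound, and only the wording needs attention. The sentence also cites a methods source that is not available here, so the intended scale cannot be settled from the article. An analyst would probably pool the raw coefficients anyway.

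Part of this stands: the intention may well have been correct. But the text does not say so. The same sentence covers the slope, which relates log-odds to log-odds and so has no log-odds unit; the reading can only be stretched to it as another logistic regression coefficient. The word *again* does not help, because the c-statistic is pooled by median and interquartile range, with neither a log scale nor Rubin's rules.

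A reader might infer three stronger points, which the article does not support:

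- *The slope fails too.* It does not in practice, as Step 4 shows.
- *The pooled value will be biased towards under-prediction because software drops undefined logarithms.* That assumes a coding error which the plan neither describes nor implies.
- *The pooled coefficient decides which models receive an intercept update.* The Updating section refers only to miscalibration and names no criterion. The LOESS plots on stacked data involve no log pooling and would show over-prediction.

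The scope is also limited. The rule applies to four of the eight models and only if data are multiply imputed, which is anticipated but not fixed. Discrimination, plots and decision curves are untouched.

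**Conclusion.** The concern holds for calibration-in-the-large. As written, the pooling rule cannot be carried out at the article's own target value of 0 or for an over-predicting model. That conclusion needs no assumption beyond the definition of the coefficient.

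The frequencies are illustrations in the plan's sample-size scenario. About half of single estimates from a well-calibrated model are at or below 0. With 50 imputations, at least one is at or below 0 in 69% to 88% of analyses, under assumed between-imputation fractions of 5% to 30%. For the slope, the log is needless but not undefined.

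This is an incorrect statement of method, not a detail left to a later plan, because a fuller analysis plan would have to contradict the sentence. The consequence is moderate: a prespecified rule for one reported measure is not executable. The article gives no ground for concluding that results will be biased or update decisions wrong.

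**What to change.** Replace the pooling sentence with: *The calibration-in-the-large coefficient and the calibration slope, with their standard errors, are pooled untransformed with Rubin's rules; if an observed/expected ratio is reported, it is pooled as log(O/E).* Delete *again*.

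If the log-odds reading was intended, this wording states it. The cost is one sentence, with no change to data, sample size or any other analysis.

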#### Decision curve analysis

Decision curve analyses will be performed to quantify the net benefit achieved by each model for predicting the originally intended endpoint across a range of risk thresholds ranging from zero to one [37].

#### Updating

Prediction models showing miscalibration will be adjusted using an intercept update, and predictive performance will be re-assessed for the recalibrated model.

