**Methods:**

Based on a living systematic review of COVID-19 prediction models, we identified eight prognostic models predicting the risk of mortality in adults with a COVID-19 infection (five COVID-19 specific models: GAL-COVID-19 mortality, 4C Mortality Score, NEWS2 + model, Xie model, and Wang clinical model and three pre-existing prognostic scores: APACHE-II, CURB65, SOFA). These eight models will be validated in six different cohorts of the Dutch older population (three hospital cohorts, two primary care cohorts, and a nursing home cohort). All prognostic models will be validated in a hospital setting while the GAL-COVID-19 mortality model will be validated in hospital, primary care, and nursing home settings. The study will include individuals ≥ 70 years of age with a highly suspected or PCR-confirmed COVID-19 infection from March 2020 to December 2020 (and up to December 2021 in a sensitivity analysis). The predictive performance will be evaluated in terms of discrimination, calibration, and decision curves for each of the prognostic models in each cohort individually. For prognostic models with indications of miscalibration, an intercept update will be performed after which predictive performance will be re-evaluated.

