#### Sensitivity analysis

Two sensitivity analyses will be performed to assess the variation in the predictive performance of the eight COVID-19 prognostic models when implemented in different time periods: January 2021 to December 2021 and March 2020 to December 2021. Additionally, predictive performance in estimating the 90-day mortality risk will be evaluated in cohorts that have data available on this outcome (CliniCo, COVID-PREDICT, PHARMO, JHN/ANH/AHA, Ysis).

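### An intercept update is the only remedy planned for any miscalibration; for the four equation models it cannot correct the slope, and three re-assessed measures are fixed in advance if the same cohort is used

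*Protocol article*

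**What the plan says.** The rule stands twice in the protocol article. The Updating section reads: "Prediction models showing miscalibration will be adjusted using an intercept update, and predictive performance will be re-assessed for the recalibrated model". The abstract's Methods paragraph has the same rule: "For prognostic models with indications of miscalibration, an intercept update will be performed after which predictive performance will be re-evaluated". Neither place separates a wrong overall level of risk from a wrong slope, and neither names a slope update.

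The abstract also says what performance means: "The predictive performance will be evaluated in terms of discrimination, calibration, and decision curves for each of the prognostic models in each cohort individually". The section Assessment of predictive performance supplies the measures:

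- discrimination: "Discrimination will be assessed in all models by quantifying the area under the receiver operating characteristic curve, i.e., c-statistic";
- calibration by plot: "Calibration will be assessed by visualizing the calibration of expected versus observed risk using LOESS-smoothed plots on stacked imputed data sets";
- calibration by number, for the GAL-COVID-19 mortality, NEWS2+, Xie and Wang clinical models only: "For these models, calibration will be assessed in terms of the calibration-in-the-large coefficient and calibration slope".

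The Decision curve analysis section adds net benefit over thresholds from zero to one. The Statistical analysis section says that performance is evaluated separately in each cohort. No held-out cohort, held-out period or resampling is named for the re-assessment of updated models. The Sensitivity analysis section does plan to assess performance in two further periods, "January 2021 to December 2021 and March 2020 to December 2021", but does not link them to updating.

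**The concern.** The trigger is wider than the remedy. A slope away from 1 is miscalibration by the article's own measures, so it sets off the update, but an intercept shift cannot act on it.

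This bears on the purpose of the study. The abstract's Discussion wants to learn how far models need tailoring for older people, and the Background expects underperformance because of frailty and multimorbidity. Such conditions may change how strongly predictors relate to death, not only the average risk. The Sample size section is itself built around the precision of the calibration slope. With an intercept update alone, the study cannot show what would be gained by correcting the slope as well. It therefore cannot separate models that need only a new baseline risk from models whose predictions also need rescaling.

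The second part concerns the re-assessment. If it uses the cohort in which the intercept was estimated, several of the tabulated results follow from the method and say nothing about the updated model.

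**Working it through.** The article gives no figure for this point, so there is none to reproduce. The check is algebra, followed by simulation.

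**Algebra.** Let LP be a model's linear predictor. The update is LP* = LP + d, where d is the maximum likelihood intercept of a logistic model with LP as offset.

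1. *c-statistic.* LP_i > LP_j exactly when LP_i + d > LP_j + d. Ranks do not change, so the c-statistic does not change.
2. *Slope.* logit P(y=1) = a + b·LP* = (a + b·d) + b·LP. The constant is absorbed by the intercept, so b does not change.
3. *Calibration-in-the-large.* d solves Σ[y − expit(LP + d)] = 0. Refitting the intercept with LP* as offset in the same data gives 0, and observed/expected is 1. This is exact when d is estimated within each imputed dataset, and approximate when one pooled d is used.
4. *Net benefit and LOESS plot.* NB(t) = TP/n − (FP/n)·t/(1 − t), where patients with predicted risk ≥ t count as positive. This depends on absolute risk, as does the plot, so both change.

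**Simulation.** From the Sample size section: LP ~ N(−3.9, 1) (mean risk 0.0309, in line with the stated 3%) and 754 patients, used here only as a cohort size. Assumed: true slopes of 0.6 and 1.0, the intercepts below, and a second distribution, N(−1, 1), for a setting with higher mortality.

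- A: LP ~ N(−3.9, 1); true logit = −3.9 + 0.8 + 0.6(LP + 3.9); 41 events.
- B: LP ~ N(−1, 1); true logit = −1 + 0.8 + 0.6(LP + 1); 359 events.
- C: LP ~ N(−1, 1); true logit = −1 − 0.5 + 1.0(LP + 1); 158 events.

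| | A before → after | B before → after | C before → after |
|---|---|---|---|
| c-statistic | 0.6326 → 0.6326 | 0.6594 → 0.6594 | 0.7350 → 0.7350 |
| Slope | 0.470 → 0.470 | 0.620 → 0.620 | 0.975 → 0.975 |
| Calibration-in-the-large | 0.699 → 0 | 0.847 → 0 | −0.571 → 0 |
| Observed/expected | 1.895 → 1.000 | 1.530 → 1.000 | 0.698 → 1.000 |

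Net benefit does move:

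- A: 0.0028 → 0.0122 at threshold 0.05, but 0.0010 → −0.0028 at threshold 0.10.
- B: 0.280 → 0.340 at threshold 0.2, and 0.191 → 0.249 at threshold 0.3.

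In C, where the true slope is 1, the intercept update removes essentially all the miscalibration.

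**What remains when the slope is wrong.** A further constructed case has n = 20,000, LP ~ N(−0.5, 1.2), true logit = 0.4 + 0.6·LP and about 52% mortality. After updating, calibration-in-the-large is 0 and the slope is still 0.605. In the lowest tenth of risk the prediction is 13.0% and the observed rate 24.0%. In the highest tenth the figures are 89.5% and 79.4%.

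**Separate data.** With d estimated in one half of the cohort and tested in the other, calibration-in-the-large was 0.24 (A), 0.03 (B) and −0.11 (C). It is then a result and not an identity. Logistic recalibration on intercept and slope also gives a slope of 1.000 by construction in its own fitting data, so that update needs separate data as well.

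**The case against.** A reader might infer that the re-assessment shows nothing. The article does not support that. Its performance measures include decision curves and LOESS plots, both of which change after an intercept update. How much net benefit is recovered by correcting baseline risk alone is a useful result.

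A reader might also infer that slope miscalibration would be hidden behind the word recalibrated. Nothing says so. The slope is to be reported with a 95% CI, so an unchanged slope of 0.6 and a bent curve would remain visible. What is missing is the correction.

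A third inference, that post-update net benefit would be seriously optimistic, is not borne out in general. In the constructed case with 52% mortality, at n = 754, same-data net benefit exceeded its value in new patients by 0.001 to 0.002 at thresholds 0.2, 0.3 and 0.5, against a gain from updating of about 0.02 to 0.03. At about 4% events the optimism was about 0.0007 at thresholds 0.03 and 0.05, which matters more there because the gain is itself small.

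Other limits stand:

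- Use of the same data is inferred. A fuller analysis plan, not shown, may settle it.
- The argument about slope and calibration-in-the-large covers only the four equation models; for the points-based scores neither measure is planned.
- Intercept-only updating is an established and parsimonious choice in a validation study, and it suffices when the slope is close to 1.

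None of this removes the mismatch. The remedy is stated twice, without condition, and cannot act on one of the two numerical faults that trigger it.

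**Conclusion.** The point holds for the four equation models. That the intercept update leaves the c-statistic and slope unchanged is certain. That calibration-in-the-large becomes zero is certain in the data used to estimate the intercept (approximately so with one intercept pooled over imputations). The conclusion that these three measures are predetermined also assumes re-assessment in the updating cohort, as the text naturally reads. The LOESS plot and net benefit remain informative, as apparent performance.

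The size for this study is unknown, because the article gives no expected slope. It ranges from practically nothing if the slope is near 1 to errors of about 10 to 11 percentage points in the outer tenths of risk in the constructed case with slope 0.6 (24.0 − 13.0 = 11.0; 89.5 − 79.4 = 10.1). The latter illustrates the algebra and is not a forecast. The validation of the original models is untouched; the weakness is confined to what can be learned from updating.

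**What to change.** In the Updating section:

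1. Keep the intercept update. For the four equation models, where the 95% CI of the calibration slope excludes 1, also fit logistic recalibration (intercept and slope). Report it beside the intercept-only update, with its own LOESS plot and decision curve. In cohorts with few deaths the interval will be wide, so an interval that includes 1 should not be read as proof that the intercept update is enough.
2. State in which data the update is estimated and in which it is re-assessed. Label same-data results as apparent performance.
3. Where feasible, evaluate the updated model in another cohort of the same setting. There are three hospital cohorts and two primary care cohorts; the single nursing home cohort has no counterpart.
4. As a secondary check, apply the 2020 update to January–December 2021, a period already in the sensitivity analysis. The Challenges and limitations section expects change over time from variants, medical management and vaccination, so a poor result in 2021 would not by itself show that the update was bad.

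The cost is a little more analysis on data already planned, and a second updated version to report for some models. Results outside the fitting data may also look less favourable.
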